## Abstract

**Background:**

Case management has emerged as a promising alternative approach to supplement traditional one-on-one sessions between patients and doctors for improving the quality of care in chronic diseases such as coronary heart disease (CHD). However, data are lacking in terms of its efficacy and cost-effectiveness when implemented in ethnic and low-income populations.

**Methods:**

The Stanford and San Mateo Heart to Heart (HTH) project is a randomized controlled clinical trial designed to rigorously evaluate the efficacy and cost-effectiveness of a multi-risk cardiovascular case management program in low-income, primarily ethnic minority patients served by a local county health care system in California. Randomization occurred at the patient level. The primary outcome measure is the absolute CHD risk over 10 years. Secondary outcome measures include adherence to guidelines on CHD prevention practice. We documented the study design, methodology, and baseline sociodemographic, clinical and lifestyle characteristics of 419 participants.

**Results:**

We achieved equal distributions of the sociodemographic, biophysical and lifestyle characteristics between the two randomization groups. HTH participants had a mean age of 56 years, 63% were Latinos/Hispanics, 65% female, 61% less educated, and 62% were not employed. Twenty percent of participants reported having a prior cardiovascular event. 10-year CHD risk averaged 18% in men and 13% in women despite a modest low-density lipoprotein cholesterol level and a high on-treatment percentage at baseline. Sixty-three percent of participants were diagnosed with diabetes and an additional 22% had metabolic syndrome. In addition, many participants had depressed high-density lipoprotein (HDL) cholesterol levels and elevated values of total cholesterol-to-HDL ratio, triglycerides, triglyceride-to-HDL ratio, and blood pressure. Furthermore, nearly 70% of participants were obese, 45% had a family history of CHD or stroke, and 16% were current smokers.

**Conclusion:**

We have recruited an ethnically diverse, low-income cohort in which to implement a case management approach and test its efficacy and cost-effectiveness. HTH will advance the scientific understanding of better strategies for CHD prevention among these priority subpopulations and aid in guiding future practice that will reduce health disparities.

## Background

Coronary heart disease (CHD) affects 13 million Americans and is estimated to have cost the US 142 billion dollars in 2005 [1]. The current primary care delivery model lacks a multidisciplinary infrastructure that is conducive to effective management of multiple CHD risk factors [2]. The growing strain of chronic disease management on the health care system leaves physicians little time for preventive care [3], which paradoxically is indispensable for the treatment and prevention of many chronic diseases including CHD. While CHD affects every racial/ethnic group and social class, ethnic minorities and persons of low socioeconomic status (SES) disproportionately bear the burden of CHD and its major risk factors [1,4], These population subgroups also are more likely to receive substandard cardiac care compared with whites and individuals of higher SES [5]. Accelerating the translation of research into community-based practice and enhancing health impact in disparate populations have been identified as strategic imperatives for the elimination of inequities in cardiovascular health [6].

Alternative approaches are needed to supplement traditional one-on-one sessions between patients and doctors. One such approach is integrated care delivered through case management (CM). Case management is a comprehensive, longitudinal approach that involves a multidisciplinary team of health care providers, such as physicians, nurses and dietitians, who simultaneously intervene to reduce multiple risk factors for a disease, such as CHD. Randomized clinical trials have established the efficacy of intensive case management intervention to reduce multiple cardiovascular risk factors among predominantly white, high-risk patients [7-10]. Only recently has this therapeutic approach been tested among ethnic minorities, where it was found to be effective [11]. Researchers have urged greater implementation of case management [12].

Chronic disease management for ethnic minorities of low-SES represents unique and difficult challenges for local health care systems, many of which are overburdened by a complex clinical load and have a primary care delivery model that is not well designed to provide intensive chronic disease management.

The Stanford and San Mateo Heart to Heart (HTH) project is designed to conduct a randomized controlled clinical trial that rigorously evaluates the efficacy and cost-effectiveness of a case management intervention in reducing cardiovascular risk among patients of the San Mateo County Medical Center (SMMC) in California, U.S.A. Based on outcomes data available through the clinical trial, HTH staff will then facilitate implementation of the HTH case management model as an ongoing disease management program within SMMC. This report details the study design, methodology, and baseline sociodemographic, clinical and lifestyle characteristics of 419 randomized participants. We expect participants to have sociodemographic characteristics that differ significantly from those of the San Mateo County and U.S. adult populations. We also anticipate that participants will possess clinical and lifestyle risk factors that predict elevated risk of future cardiovascular events and that these risk factors can be modified through intense medical and/or lifestyle interventions.

## Methods

The study was approved by the Stanford Institutional Review Board (IRB) and an independent IRB responsible for reviewing study protocols for the San Mateo Medical Center (SMMC).

### Study setting

San Mateo County in California is a study in contrasts – although this mostly suburban county includes some of the most expensive housing in the nation, it has a sizable population of lower-SES persons with demographic characteristics comparable to urban areas. As of 2004, the racial composition of San Mateo County was 62% White, 26% Asian/Pacific Islander, and 4% Black. Twenty-two percent of the population self-identified as Hispanic and 32% as foreign-born [13]. Within San Mateo County, heart disease is the leading cause of death (29% of all deaths during 1997–2001) while stroke is third [14]. In 2004, 7% of the adult population had diabetes with the highest prevalence (15%) among persons aged 65 and older. In addition, 86% of San Mateo County adult residents had reported at least one cardiovascular risk factor, *e.g.*, 75% for overweight and obesity, 55% for physical inactivity, 26% for hypertension, 25% for hyperlipidemia, and 12% for smoking. As a branch of the county government, the SMMC serves a significant portion of the county population that has low SES and lacks private health insurance. The SMMC has approximately 106 physicians per 100,000 people, whereas the national average was 289/100,000 in 2000.

### Study design

HTH is a 5-year project that consists of a randomized controlled clinical trial in the first 4 years and a transition phase in the last year. The 2-armed clinical trial (Immediate vs. Delayed Intervention) was designed to enroll 400 patients. In an intention-to-treat analysis, this sample size yields 87% power to detect a mean change of 5 points in the Framingham risk score, with an SD of 10, at an α level of 0.01 after accounting for a 25% loss to follow-up.

Participants in both intervention groups continue to receive usual medical care throughout the study period. In addition, participants randomized to Immediate Intervention receive intensive case management for CHD risk reduction for 15 months and then a maintenance program for a minimum of 12 months to assess the durability of initial intervention changes. Participants randomized to Delayed Intervention serve as control for Immediate Intervention patients for the first 15 months and then receive intensive case management for 15 months. The switching-over design not only addresses ethical concerns about withholding treatment from half the study sample, but will also enable us to assess whether the intervention had equal impact whether provided to a naïve population or to a group followed in usual care for 15 months. We will compare change in CHD risk from baseline to 15 months for Immediate Intervention with that from 15 months to 30 months for Delayed Intervention. Similar magnitudes of change in CHD risk between the two study arms would imply that the Delayed Intervention arm was not notably contaminated by the intervention and measurement process and that no noteworthy differences were caused by the 15-month difference in time *per se*.

Immediate Intervention patients who complete their 12-month maintenance period and Delayed Intervention patients who complete their 15-month case management period remain under maintenance case management until they are fully transitioned back to the care of the SMMC in the last year of the project. In addition to patient transition, we will also transition the HTH case management model, as guided by outcomes data from the clinical trial, into an ongoing disease management program operated by SMMC. By including this transition phase, we will be able to assure continuity in patient care and also test the feasibility and effectiveness of implementing our intervention in a community practice setting.

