### Statistical analysis and hypothesis testing

The primary hypothesis of the trial is that Immediate Intervention participants will experience greater reductions in 10-year CHD risk based on Framingham risk probability (primary outcome) than will Delayed Intervention participants. To test the primary hypothesis, we will compare Immediate Intervention participants relative to Delayed Intervention participants in a random-effects regression using SAS PROC GLIMMIX. The dependent variable will be the standardized Framingham risk score at 15-month follow-up. Initially, covariates will be limited to the baseline risk score and intervention status. So we will model participant i (i = 1, 2,..., n_jk_) under the care of physician j within clinic k as:

(1)     Risk_1ijk _= b_0 _+ b_1_Risk_0ijk _+ b_2_Int_ijk _+ α_j _+β_k _+ e_ijk_

where **Risk_1ijk _**is the standardized risk score for the i-th participant at 15 months (time 1) cared for by physician j in clinic k, **Risk_0ijk _**is the risk score at baseline (time 0), **Int_ijk _**is the intervention vs. control status of the i-th participant in the same clinic and under the same physician, **b_0 _**is a constant term, **b_1 _**is the coefficient associated with impact of baseline risk, and **b_2 _**is the coefficient associated with the impact of the intervention. **α_j _**represents the random effect caused by physician j and **β_k _**is the random clinic effect. The error term **e_ijk _**follows normal distribution, N(0, σ^2^). The analysis will be conducted on an intention-to-treat basis. The risk scores of participants lost to follow-up will be set to the baseline or interim values. Alternative methods for handling missing data, such as multiple imputation, may be used if appropriate. Our primary hypothesis will be confirmed if the coefficient associated with the intervention (**b_2_**) is significantly less than 0, implying that the intervention decreased CHD risk scores independent of the baseline level.

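### Equal impact, no notable contamination and no time effect are to be inferred from similar-looking changes in the two arms, without regard to the precision of their difference

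*Protocol article*

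**What the plan says.** In the Study design section, the protocol article gives one purpose of the switch-over, which is to "enable us to assess whether the intervention had equal impact whether provided to a naïve population or to a group followed in usual care for" (the usual-care phase lasts 15 months). The contrast is then named: "We will compare change in CHD risk from baseline to 15 months for Immediate Intervention with that from 15 months to 30 months for Delayed". What is to be concluded from it is stated next: "Similar magnitudes of change in CHD risk between the two study arms would imply that the Delayed Intervention arm was not notably contaminated". A second conclusion, about calendar time, is drawn from the same finding: "no noteworthy differences were caused by the 15-month difference in time".

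The article does not say how close the two changes must be, or how the uncertainty of their difference enters the judgement. The section on statistical analysis and hypothesis testing gives one explicit decision rule, for another question, and it begins "Our primary hypothesis will be confirmed if the coefficient associated with the intervention"; the condition is that the estimate falls significantly below zero. The only sample-size statement also concerns detecting a difference. The planned size is given in the words "was designed to enroll 400 patients". The power claim is that "this sample size yields 87% power to detect a mean change of 5 points in the Framingham risk score, with an SD of 10". Its conditions are a significance level of 0.01 and an allowance for losing 25% of patients.

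**The concern.** Concluding that two effects are equal, or that contamination and time effects were negligible, is a claim of sameness. Such a claim needs evidence that the difference is small, so an upper limit on it is required. Two point estimates that look alike do not give that limit, and neither does a non-significant difference. Both depend on how precisely the difference was measured. If the judgement rested on non-significance, fewer patients remaining at 30 months would make sameness easier to claim.

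The conclusion would bear on contamination, which the Randomization section names as the drawback of randomising patients within clinics. It would also be part of the outcome evidence at hand when the model is handed over to the county system. The problem is separate from any bias in comparing different calendar periods: even an unbiased contrast would not support the inference as worded.

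**Working it through.** **Inputs from the article.** 400 enrolled, so 200 per arm if allocation is 1:1 (212 and 207 were randomised); design effect 5 points; SD 10; alpha 0.01; 25% loss, leaving 150 per arm.

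**Assumptions.** SD 10 is the SD of each arm's 15-month change. A non-significant two-sided difference test stands in for the undefined word similar. A halved effect means a gap of 5 − 2.5 = 2.5 points. Normal approximation, no clustering by physician.

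**The plan's own power figure.** It belongs to the superiority comparison.
- 150 per arm, difference 5, two-sided 0.01: 96.0%. This does not match the stated 87%.
- 200 per arm, with 25% of patients contributing zero change: difference 0.75 × 5 = 3.75, SE = 10 × √(2/200) = 1.00, power 88.0% (87.7% by noncentral t). This is close to 87%.
- 112 per arm (25% loss taken twice), difference 5: 87.8% (87.2% by noncentral t). Also close.

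The article does not say which was used, so results are shown for more than one reading.

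**Precision of the equal-impact contrast.** SE = SD × √(2/n) = 10 × √(2/150) = 1.155 points. The 95% half-width is 1.96 × 1.155 = 2.26 points, nearly half the design effect.

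**Chance that a true gap is non-significant.** With z the two-sided critical value, P = Φ(z − gap/SE) − Φ(−z − gap/SE). For 150 per arm and a gap of 2.5, gap/SE = 2.165. At alpha 0.05, Φ(1.960 − 2.165) = Φ(−0.205) = 0.42. At alpha 0.01, Φ(2.576 − 2.165) = Φ(0.411) = 0.66. The second term is negligible.

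| Setting | True gap | alpha 0.05 | alpha 0.01 |
|---|---|---|---|
| Halved effect, SD 10, 150/arm | 2.5 | 42% | 66% |
| Halved effect, SD 10, 200/arm, no loss | 2.5 | 30% | 53% |
| Halved effect, diluted, 200/arm | 1.875 | 53% | 76% |
| Halved effect, SD 10, 112/arm | 2.5 | 54% | 76% |
| Halved effect, SD 7 (assumed), 150/arm | 2.5 | 13% | 30% |
| Lost effect, SD 10, 150/arm | 5 | 0.9% | 4.0% |
| Lost effect, diluted, 200/arm | 3.75 | 3.7% | 12% |

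**What an interval-based rule would deliver.** Take an illustrative margin of ±2.5 points, a 90% confidence interval and truly identical effects. Power = 2Φ(margin/SE − 1.645) − 1.
- SD 10, 150 per arm: 2Φ(2.165 − 1.645) − 1 = 2Φ(0.520) − 1 = 0.40.
- SD 7, 150 per arm: SE = 7 × √(2/150) = 0.808; 2Φ(3.093 − 1.645) − 1 = 2Φ(1.448) − 1 = 0.85.

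**The case against.** The strongest reply is that the article nowhere says a non-significant difference will be read as similar. It speaks of magnitudes, which is language about estimates. That stands, and so every rate above is conditional. On an estimate-based reading the error is smaller. If similar meant observed changes within 1.25 points of each other (assumed), a true 2.5-point gap would pass in Φ(−1.25/1.155) − Φ(−3.75/1.155), or about 14%, of trials. Such a rule would still take no account of precision.

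Second, SD 10 may be the spread between patients and not the SD of change. The baseline standard errors by sex in Table 4 give SDs of 1.0 × √145 = 12.0 for men and 0.5 × √274 = 8.3 for women, so about 10 overall. With a baseline to follow-up correlation of 0.75 (assumed), the SD of change would be 10 × √(2 × 0.25) = 7.1. The SD 7 row is therefore plausible.

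Third, the comparison is neither the primary hypothesis nor among the secondary hypotheses listed as examples. The Randomization section offers other safeguards against contamination: separate case managers and scheduling, and an analysis of correlation within physicians' practices. This limits the weight of the point. A margin might also be set in an analysis plan that is not shown. That would answer a complaint of mere omission, but the article states the inference itself, and the inference can be judged as written.

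A reader might go further and infer that even a complete loss of effect in one arm could readily pass as equal. The plan's own figures do not support this: the chance is about 1–4%, or at most 12% in the settings tabulated. It reaches 42–66% only if the true effect is 2.5 points, half of what was planned for.

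**Conclusion.** The point holds in a limited form. The article draws equal impact, no notable contamination and no noteworthy time effect from similar magnitudes of change, without bringing in the precision of the difference. That reasoning is unsound as worded, because look-alike estimates can reflect imprecision as well as sameness.

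The size depends on a rule the article does not give. If non-significance is the criterion, a halved effect would pass in 42% to 66% of trials at SD 10 and 150 per arm, and in 13% to 30% at SD 7. More loss by 30 months would raise these rates. The primary superiority test is not affected. The comparison is a supporting one, so the correction is worth making but does not threaten the trial's main conclusion.

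**What to change.** In the Study design section, replace the sentence that reads sameness from similar magnitudes with a rule of this kind:

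- Estimate the difference between the two 15-month changes and report it with its confidence interval (90% if a two one-sided tests approach at 5% is used).
- Claim equal impact only if the whole interval lies within a margin that the sponsor justifies and states in advance. The ±2.5 points used above, half the design effect, is only an illustration.
- Otherwise report the comparison as inconclusive and supportive only. Do not infer equality, or absence of contamination, from look-alike estimates or from a non-significant difference.

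The change needs a few sentences and no new patients or data. Its cost is that the claim becomes harder to make. With the illustrative margin, identical effects and 150 per arm, the rule would succeed in about 40% of trials at SD 10 and about 85% at SD 7. The sponsor should say this openly when setting the margin.

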### Recruitment

Between October 2003 and April 2005, 1005 patients were referred by physicians at four SMMC outpatient clinics located in Menlo Park, Redwood City, South San Francisco, and Daly City. These four clinics were chosen for geographic proximity, accommodating clinic environment, sufficient patient volume, diverse patient demographics, and established adult primary care services. All data acquisition and case management visits took place at the clinic where the patient usually receives his/her primary care.

Physicians at the study clinics were instructed to refer male and female patients between the ages of 35 and 85 who had CHD, CHD risk equivalents (*i.e.*, abdominal aortic aneurysm, peripheral vascular disease, carotid artery disease, or diabetes mellitus), or moderately to severely elevated levels of major CHD risk factors. We were unable to contact 257 of the 1005 referred patients and an additional 142 declined participation (Figure 1). We screened the remaining 596 patients by phone or at the baseline visit and excluded 143 patients for failing to meet the exclusion criteria. These criteria identify patients with circumstances that may severely limit their ability complete the study protocol or that may confound results of the study. The footnotes in table 1 list percentages by exclusion criteria. During the same phone call, those not excluded were scheduled for a baseline visit. Table 1 enumerates study inclusion and exclusion criteria. Consent forms were available in English and Spanish and the patient's informed consent was obtained before the start of the baseline visit. For patients who spoke a language other than English or Spanish, a family member over the age of 18 or a SMMC staff member served as interpreter. As part of the baseline evaluation, biophysical measures were obtained that further excluded 44 patients not meeting inclusion criteria.

**Table 1 T1:** Inclusion and exclusion criteria.

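### Similar changes in Immediate months 0–15 and Delayed months 15–30 do not show that the Delayed arm was uncontaminated or that timing made no difference

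*Protocol article*

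**What the plan says.** In the Protocol article, Study design, Delayed Intervention patients "serve as control for Immediate Intervention patients for the first 15 months and then receive intensive case management for 15 months". The section then plans to "compare change in CHD risk from baseline to 15 months for Immediate Intervention with that from 15 months to 30 months for Delayed" Intervention patients, and draws two inferences from that one contrast. The first is: "Similar magnitudes of change in CHD risk between the two study arms would imply that the Delayed Intervention arm was not notably contaminated", where both case management and the act of measuring are named as possible sources. The second is that "no noteworthy differences were caused by the 15-month difference in time" as such. The contrast is also meant to show whether the intervention works equally well in newly enrolled patients and in patients already followed for 15 months.

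Other sections bear on this:
- Randomization concedes that patient-level allocation allows contamination, expects it to be modest, says that it would bias towards the null, and proposes intra-class correlation within physicians' practices to assess it.
- Delayed intervention describes what control patients received at the start (handouts and a sheet of their own readings beside ideal values) and a letter on guideline goals sent to all primary care physicians.
- Statistical analysis and hypothesis testing makes the primary test the concurrent randomized comparison at 15 months, adjusted for baseline risk.

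**The concern.** Contamination matters because it lowers risk in the control group while that group is serving as control, in Delayed months 0–15. The planned check uses Delayed months 15–30. It sees earlier spillover only indirectly, if that spillover has reduced what case management can still achieve.

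The two changes also come from different calendar periods. After month 15 the Delayed arm receives case management and the Immediate arm is in maintenance, so no untreated group shows what would have happened in months 15–30. The starting points differ as well: at the baseline visit "biophysical measures were obtained that further excluded 44 patients not meeting inclusion criteria", whereas no such selection is made at month 15.

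At stake is a secondary conclusion. Under the stated rule, a trial whose 15-month effect had been diluted could be reported as uncontaminated, and the equal-impact question could be answered from a contrast that mixes effect and period.

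**Working it through.** **Inputs.** From Study design: N = 400, a 5-point effect, SD 10, α = 0.01, 25% loss. Equal allocation and a two-sided test are assumed. The spillover size c and the share λ of it that uses up later benefit are not in the article; both are varied.

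**1. The article's own figure.** It states that "this sample size yields 87% power to detect a mean change of 5 points in the Framingham risk score". With 200 per arm and an intention-to-treat effect diluted by 25% loss, 0.75 × 5 = 3.75, SE = 10·√(2/200) = 1.00 and power = Φ(3.75 − 2.576) = 88.0% (87.7% with the t distribution), close to the stated 87%. Using 150 completers per arm and the full 5 points gives 96.0%. The planning figures can therefore be used for illustration.

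**2. What the contrast contains.** Let E be the effect, and T1 and T2 everything else that moves risk in months 0–15 and 15–30 (usual-care trend, regression to the mean, ageing in the score).
- Immediate, 0–15: −E + T1
- Delayed, 0–15: −c + T1
- Randomized 15-month contrast: −(E − c)
- Delayed, 15–30: −(E − λc) + T2
- Planned contrast (Delayed 15–30 minus Immediate 0–15): λc + (T2 − T1)

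The planned contrast is zero whenever λc = T1 − T2. That does not require c = 0, and it does not require T1 = T2.

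**3. Additive spillover (λ = 0), no time effect.** Both changes equal −5 for any c. With c = 2 the randomized contrast is 5 − 2 = 3; with c = 3 it is 2. A test of the planned contrast at two-sided 0.05 calls the changes different 5% of the time, its false-positive rate.

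**4. Displacing spillover (λ > 0), no time effect.** With 200 × 0.75 = 150 per arm and a change SD of 10, SE = 10·√(2/150) = 1.155 and the 95% half-width is 1.96 × 1.155 = 2.26 points, or 2.26/5 = 45% of the planned effect. Power at two-sided 0.05 is Φ(λc/SE − 1.96) + Φ(−λc/SE − 1.96):

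| Spillover c | λ = 0.5 | λ = 1 |
|---|---|---|
| 1 point | 7% | 14% |
| 2 points | 14% | 41% |
| 3 points | 26% | 74% |

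**5. Sensitivity to the SD.** If 10 is the SD of the score and not of the change, the change SD is 10·√(2(1 − r)). For an assumed baseline-to-follow-up correlation r of 0.6 to 0.8 this is 8.9 to 6.3. With 150 per arm the half-width becomes 2.0 to 1.4 points, and power for c = 2, λ = 1 becomes 49% to 78%. Step 3 does not depend on the SD.

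**6. Time effects.** If c = 2 and λ = 1 but months 15–30 carry an extra 2-point fall (T2 − T1 = −2), the contrast is 2 − 2 = 0: similar changes, with both contamination and a time effect present.

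Regression to the mean works the other way. It enters mainly T1, so it makes the Immediate fall larger and imitates displacing contamination. As an upper bound, removing the lowest 44/(419 + 44) = 9.5% of a normal score shifts the mean by 0.187 SD. With a score SD of 10 that is 1.87 points, of which 1.87 × (1 − r) regresses: 0.37 points at r = 0.8 and 0.75 at r = 0.6. The true amount is likely smaller, because eligibility used components such as BMI and triglycerides that are not listed as inputs to the risk score.

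**The case against.** The strongest reply is that this is a supporting interpretation. The primary test is concurrent and randomized and makes no use of the contrast. The Randomization section discloses contamination, describes safeguards, notes that its bias is conservative, and names a separate intra-class correlation assessment. All of that stands, and it limits the consequence. It does not repair the inference: intra-class correlation describes clustering within practices and does not by itself measure how much of the intervention reached control patients.

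A reader might infer several stronger points that the article does not support:
- *The contrast is blind to contamination.* That is true only if spillover is purely additive. Three points of fully displacing spillover would show as a difference about 74% of the time under step 4.
- *The plan would blame contamination for any difference.* The article says only what similarity would mean. By naming timing as a second factor, it leaves a difference open to either cause.
- *Regression to the mean dominates the contrast.* The bound of 0.37 to 0.75 points lies well inside the half-widths above, and it uses 10 as the score SD, whereas step 4 uses 10 as the change SD. Both cannot be taken as given.
- *The missing margin for similarity is a defect.* A margin and model details commonly sit in a statistical analysis plan, and the article does not say that non-significance will be read as similarity.

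**Conclusion.** The inference is wrong as written. Similar changes cannot exclude contamination, and they cannot exclude a time effect, because the contrast measures λc + (T2 − T1) and neither part can be isolated from it. Under additive spillover, similarity is expected whatever the amount: −5 and −5 beside a randomized contrast of 3 instead of 5 when c = 2. Under full displacement, 2 points would be detected about 41% of the time with 150 per arm and a change SD of 10, or 49% to 78% if the change SD is 8.9 to 6.3. Spillover sizes, λ and r are assumptions; the logical point does not depend on them. A difference between the two changes may hint at contamination. What is affected is the secondary conclusion on contamination, timing and equal impact. The primary 15-month result is not affected.

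**What to change.** In Study design, replace the implication with wording such as: *similar changes would be consistent with, but cannot establish, the absence of notable contamination or of a time effect.*

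Report the Delayed arm's own change in months 0–15, and any exposure to intervention elements in that period, as the more direct evidence. State that this change also contains usual-care trend and regression to the mean. It cannot separate them from contamination, so it should not serve both as the contamination measure and as the trend estimate.

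Present the 0–15 versus 15–30 comparison with a confidence interval, labelled as non-concurrent and supportive only, and apply the same caution to the equal-impact question.

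The cost is a change of wording and a more cautious secondary conclusion. The risk-score change comes from visits already planned; exposure to intervention elements can be reported as far as it was recorded.
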